### 9.2.4 Assessments in participants who prematurely stop the study

If patients are withdrawn because of an AE, they will undergo physical examination and additional tests (e.g. laboratory testing) according to the nature of the AE. Unless the AE causes a contraindication for the planned treatment, it will be performed as planned according to tumor board decision. A last examination for possible (additional) toxicities shall be carried out. The follow-up period ends after this last examination or when patients are dismissed from the hospital after the treatment of the AE, whichever happens last.

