#### **7.5 Criteria for withdrawal / discontinuation of participants**

Patients have the right to refuse further treatment for any reason and at any time. Patients who decide to withdraw from the trial should be asked whether they also want to withdraw their consent for their data to be used for the follow-up assessments. If allowed by the patient, the data will be used for further analysis and anonymized thereafter. For the patient's security, a last examination should be performed.

Patients may be withdrawn at any time from trial treatment at the discretion of the investigator due to a serious adverse event or based on any other relevant medical condition. The patient will then be transferred to the follow-up phase.

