## 8.2 Transoral CO2-Laser Microsurgical Cordectomy (TLM) in Arm A

### 8.2.1 Preoperative Assessment

To determine the feasibility of the surgery under general anesthesia, the anesthesia team will perform a preoperative assessment as necessary. In case of refusal due to any medical conditions, the patient has to be withdrawn from the study and treated off-protocol. A panendoscopy with assessment of transoral exposure for resection has to be performed before accrual. In case, the glottic space cannot be correctly exposed for TLM, the patient cannot be included in the study.

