## **11. STATISTICAL METHODS**

### **11.1 Hypothesis and Determination of Sample Size**

The sample size calculation is based on the primary outcome, the VHI at 6 to 24 months (averaged). Based on the literature, we consider the VHI to be comparable between TLM and traditional whole larynx radiotherapy. Therefore, the hypothesis is that there is a difference between TLM and SVCI in regard to VHI. Al-Mamgani et al. reported standard deviations for VHI ranging from 2 to 10 score points. A difference of 8 points between the two groups is regarded as clinically relevant and a conservative standard deviation of 8 points is assumed. Based on a two-sample means test, 34 patients (17 per group) are needed to detect a difference in VHI at a two-sided alpha-level of 0.05 with a power of 80%.

This sample size calculation is conservative. In the analysis, the average change from baseline to the four time points (6, 12, 18, and 24 months) will be modelled and additionally adjusted for the baseline VHI to yield more power.

No statistical criteria for the termination of the trial is defined. No interim analysis for futility or safety will be performed.

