### **11.2 Randomization and Stratification**

A probabilistic minimization technique will be used for random treatment allocation between the two treatment arms using a 1:1 ratio. The computer chooses a treatment dynamically, based on the tumor stage (Stage 0 vs. I), and VHI at baseline (<34 vs. ≥34) as two predefined stratification factors.

Allocation will be done via a dedicated website within the clinical trial management system also containing the electronic case report forms. Only system administrators who are otherwise not involved in the trial will have access to the algorithm and stored lists during the recruitment period. Investigators receive the allocation only after registration of a patient. The underlying randomization lists and details of the minimization algorithm will not be disclosed but kept securely at CTU Bern. All these measures will help to ensure concealment of allocation.

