#### **11.3.1 Datasets to be analyzed, analysis populations**

The primary analysis will follow the intention-to-treat (ITT) principle, i.e. all patients will be analyzed in the group they were originally assigned to at randomization regardless of any protocol violation.

In the per-protocol (PP) analysis, only patients that adhered to the protocol will be evaluated. Patients not receiving the allocated treatment or violating any of the inclusion criteria will be excluded from this analysis set.

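### Withdrawal rules in 8.2.1, 8.5 and 9.2.4 end or leave unscheduled the VHI follow-up of some randomized patients, in conflict with 7.5 and with the intention-to-treat analysis in 11.3.1

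*Protocol*

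**What the plan says.** The primary outcome (5.1) is the mean VHI over the visits at months 6, 12, 18 and 24. The primary analysis (11.3.1) is by intention to treat: "all patients will be analyzed in the group they were originally assigned to at randomization regardless of any protocol violation". Patients who do not receive their allocated treatment are excluded from the per-protocol set only.

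Four sections say what happens to patients who come off treatment or leave.

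- **7.5.** The investigator may take a patient off trial treatment for a serious adverse event or another relevant medical condition. "The patient will then be transferred to the follow-up phase". Patients who withdraw themselves are asked separately whether they also withdraw consent for their data to be used for follow-up.
- **8.2.1, in the Arm A section.** If the anesthesia team refuses the patient, "the patient has to be withdrawn from the study and treated off-protocol".
- **8.5.** Patients withdrawn before treatment, including those who come to prefer another treatment, are treated as the tumor board plans. Patients withdrawn once treatment has begun are asked whether data already gathered may be used. No later VHI is scheduled for either group.
- **9.2.4.** Patients withdrawn because of an adverse event have a last examination, and the planned treatment may still be given. Then: "The follow-up period ends after this last examination or when patients are dismissed from the hospital", whichever comes last.

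Section 11.4 relies on the mixed model under a missing-at-random mechanism, with multiple imputation for patients who have no outcome at all, and leaves the details to the SAP.

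**The concern.** An intention-to-treat analysis needs outcomes from randomized patients whatever treatment they receive. Sections 7.5 and 9.2.4 give opposite instructions for patients who can be the same people, because 9.2.3 counts every adverse event of grade 3 or above as serious. One site could keep collecting VHI while another stops. Under 9.2.4 a patient could even receive the allocated treatment and still have no primary outcome.

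The rule in 8.2.1 acts after randomization and in one arm only. Surgery follows randomization (8.2.2), and Table 2 notes that SVCI requires no anesthesia. An equally unfit patient allocated to Arm B would stay in the study.

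Losses of this kind may be related to outcome and may differ between arms. A missing-at-random model does not reliably correct them. If no outcome is ever observed for an Arm A patient treated off-protocol, imputation from the rest of Arm A treats that patient as though laser surgery had been done. An SAP cannot recover questionnaires that were never completed.

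**Working it through.** **1. Do the rules conflict?**

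| Patient | Section | Follow-up afterwards |
|---|---|---|
| Off trial treatment for a serious adverse event | 7.5 | Continues |
| Withdrawn because of an adverse event | 9.2.4 | Ends at last examination or discharge |
| Refused by anesthesia (Arm A only) | 8.2.1 | Withdrawn from the study; end of VHI implied, not stated |
| Withdrawn before or during treatment | 8.5 | No later VHI scheduled |
| All randomized patients | 11.3.1 | Analyzed as assigned |

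Rows 1 and 2 contradict each other for a patient with a grade 3 or higher event. Rows 2 to 4 fail to supply data that row 5 needs.

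**2. The plan's sample size.** The inputs come from 11.1 and 11.2: "A difference of 8 points between the two groups is regarded as clinically relevant"; "a conservative standard deviation of 8 points is assumed"; "random treatment allocation between the two treatment arms using a 1:1 ratio"; two-sided alpha 0.05; 17 per arm. The power of the two-sample t-test comes from the noncentral t distribution, with noncentrality d / (SD × √(1/n₁ + 1/n₂)).

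- At n = 17 per arm, the noncentrality is 8 / (8 × √(2/17)) = 2.915 on 32 degrees of freedom, and power is 80.7%. At n = 16 per arm, power is 78.1%. The plan's 17 per arm is therefore reproduced, and it contains no allowance for attrition.

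**3. Power if patients are lost, same test.**

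| Lost | Arm A only | Both arms |
|---|---|---|
| 0 | 80.7% | 80.7% |
| 1 (per arm) | 79.4% | 78.1% |
| 2 (per arm) | 78.0% | 75.3% |

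**4. Possible bias.** Let k of the 17 Arm A patients be unobserved, and let g be their mean VHI minus that of the observed Arm A patients. If the analysis in effect reproduces the observed arm mean, the group difference is wrong by (k/17) × g. The protocol gives neither k nor g, so both are assumptions: k = 1 or 2, and |g| = 0 to 16 points (up to twice the planning SD), with either sign.

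| \|g\| | k = 1 | k = 2 |
|---|---|---|
| 0 | 0 | 0 |
| 4 | 0.24 | 0.47 |
| 8 | 0.47 | 0.94 |
| 16 | 0.94 | 1.88 |

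The largest entry is 1.88 / 8 = 23.5% of the target difference. If the true intention-to-treat difference is zero and the SD is 8, the nominal 5% error rate becomes 5.1% to 6.2% for k = 1, and 5.3% to 9.9% for k = 2, over gaps of 4 to 16 points. With no gap it stays at 5%.

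**5. After the fix.** If VHI is obtained from all 17 + 17 patients, power stays at 80.7% and this source of bias is zero.

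**The case against.** The strongest reply is that the protocol already protects much of this.

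- Section 7.5 keeps treatment withdrawals in follow-up and asks separately about consent. The heading of 9.2.4 concerns patients who leave the study, who could be a different group. This stands in part, but the text of 9.2.4 defines its patients only by an adverse event and allows their planned treatment to proceed, so the overlap remains.
- Anesthesia refusal should be rare. Inclusion criterion 6 requires expected fitness for both interventions, 3.5 requires eligibility for both, and Table 2 describes medical inoperability as an exclusion. This stands as a limit on frequency.
- Section 11.4 covers missing data, and a patient lost after month 6 still contributes earlier visits. This stands, subject to the assumption described above.
- The planned model averages four visits and adjusts for baseline. If the SD of 8 is a single-visit SD (an assumption), the SD of the four-visit mean is 8 × √((1 + 3ρ)/4), where ρ is the between-visit correlation. With 15 per arm, power is then about 92% at ρ = 0.5, 82% at ρ = 0.8 and 78% at ρ = 0.9. The power loss may therefore be offset.

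Some stronger readings are tempting but not supported. A reader might infer that the intention-to-treat analysis cannot be done without bias. Bias arises only if such withdrawals occur and differ from observed patients in ways the model misses. A reader might take the sentence in 8.5 about data already gathered as ending follow-up for patients who change their mind before treatment, but it applies only to those withdrawn once treatment has begun. A reader might also assume that the lost Arm A patients would have much worse voices. Nothing in the protocol links anesthetic unfitness to VHI, and 3.1 cites studies showing no difference or better voice after radiotherapy, so the gap could be zero or reversed.

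**Conclusion.** The point holds as an internal conflict that puts primary outcome data at risk. Section 9.2.4 contradicts 7.5. Section 8.2.1 removes randomized patients from one arm only and implies, without stating it, that their VHI stops. Section 8.5 does not fill the gap. None of the three supplies what 11.3.1 needs.

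The size is modest and conditional. For 1 or 2 lost Arm A patients, the shift is 0 to about 1.9 points in either direction against a target of 8. Losing 1 or 2 patients per arm costs about 2.6 or 5.4 percentage points of power on the plan's simple test, possibly less or nothing under the planned model. The number lost and the VHI gap are assumptions. The contradiction between the sections does not depend on them. It merits correction because the remedy is cheap and uncollected VHI cannot be recovered at analysis.

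**What to change.** Reconcile 7.5, 8.2.1, 8.5 and 9.2.4 around one distinction: coming off the allocated intervention is not the same as withdrawing consent to follow-up. State once, and refer to it from each section, that every randomized patient, whatever treatment is received, continues the VHI and voice assessments at months 6, 12, 18 and 24 and the oncologic follow-up, unless consent to follow-up is withdrawn. In 8.2.1 and 9.2.4, replace the wording that removes patients from the study or closes their follow-up. In 8.5, add the continued assessment schedule. Record the reason and date for stopping the intervention separately from those for withdrawing consent.

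No treatment decision changes, and the sample size does not change because of this fix. The cost is a wording amendment and a few extra questionnaires at visits that already exist.

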### 9.3 Procedures at each visit

Procedures at each visit are described under Section 9.1 in Table 1.

## 10. SAFETY

An Adverse Event (**AE**) is any untoward medical occurrence in a patient or a clinical investigation subject which does not necessarily have a causal relationship with the trial procedure. An AE can therefore be any unfavorable or unintended finding, symptom, or disease temporally associated with a trial procedure, whether or not related to it.

**Severity:** The term “severe” is often used to describe the intensity (severity) of a specific event (as in mild, moderate or severe, or as described in CTCAE v.5.0 grades); the event itself, however, may be of relative minor medical significance (such as severe headache). This is not the same as “serious,” which is based on patient/event outcome or action criteria usually associated with events that pose a threat to patient’s life or functioning. Seriousness (not severity) serves as a guide for defining regulatory reporting obligations.

**SAE:** A **Serious Adverse Event** is defined as any untoward medical occurrence or effect in a patient, whether or not considered related to the protocol treatment, that:

- results in death;
- is life-threatening (i.e. an event in which the subject was at risk of death at the time of event; it does not refer to an event which hypothetically might have caused death if it was more severe);
- requires inpatient hospitalization or prolongation of existing patient hospitalization;
- results in persistent or significant disability or incapacity;
- is a congenital anomaly or birth defect;
- is a medically important event or reaction.

Medical and scientific judgment should be exercised in deciding whether other situations should be considered serious such as important medical events that might not be immediately life-threatening or result in death or hospitalization but might jeopardize the patient or might require intervention to prevent one of the other outcomes listed in the definition above.

**Inpatient hospitalization:** a hospital stay equal to, or greater than, 24 hours.

**Second primary malignancy** is one unrelated to the treatment of a previous malignancy (and is not a metastasis from the previous malignancy).

**Secondary malignancy** is a cancer caused by treatment for a previous malignancy (e.g., treatment with investigational agent/intervention, radiation or chemotherapy). A secondary malignancy is not considered a metastasis of the previous malignancy.

### 10.1 Exceptions

The following situations do not need to be reported as SAEs:

- Elective hospitalization for pre-existing conditions that have not been exacerbated by trial treatment.
- A hospitalization which was planned before the patient consented for study participation and where admission did not take longer than anticipated.
- A hospitalization planned for protocol related treatment or protocol related procedure as per institutional standard timelines.

- Social and/or convenience admission to a hospital.
- Medical or surgical procedure (e.g. endoscopy, appendectomy); the condition that leads to the procedure is already an (S)AE.
- Situations where an untoward medical occurrence did not occur (palliative care, rehabilitation, overdose without occurrence of an adverse event).
- Anticipated day-to-day fluctuations of pre-existing disease(s) or condition(s) present or detected at the start of the study that do not worsen.

Clinical events related to the primary cancer being studied or to the primary cancer progression are not to be reported as SAEs, even if they meet any of the seriousness criteria from the standard SAE definition, **unless** the event is more severe than expected and therefore the investigator considers that their clinical significance deserves reporting.

## 10.2 Severity assessment

The severity of all AEs (serious and non-serious) in this trial should be graded using CTCAE v.5.0.

## 10.3 Causality assessment

The investigator is obligated to assess the relationship between protocol treatment and the occurrence of each SAE following the definitions in the following table.

**Table 5: Causality assessment for SAEs**

| Relationship to the protocol treatment | Description                                                                                                                                                             |
|----------------------------------------|-------------------------------------------------------------------------------------------------------------------------------------------------------------------------|
| Not related                            | There is clearly no reasonable possibility that the protocol treatment caused the event.                                                                                |
| Unlikely                               | Any assessable reaction that does not fulfil the below conditions                                                                                                       |
| Possibly                               | Temporal relationship, but other cause also possible                                                                                                                    |
| Probably                               | Temporal relationship, condition improved after dechallenge, no other cause evident                                                                                     |
| Definitely                             | Clearly related to intervention, temporal relationship, improvement of the condition after dechallenge, recurrence after rechallenge, or other cause of treatment cause |

The investigator will use clinical judgment to determine the relationship. Alternative causes, such as natural history of the underlying diseases, medical history, concurrent conditions, concomitant therapy, other risk factors, and the temporal relationship of the event to the protocol treatment will be considered and investigated.

The decision will be recorded on the SAE form and if necessary the reason for the decision will also be recorded.

## 10.4 Expectedness assessment

The expectedness assessment is the responsibility of the sponsor of the study. The expectedness assessment will be performed against the following documents: study protocol, patient information sheet / informed consent.

## 10.5 SAE Reporting Procedure

For the time period beginning when the consent form is signed and the patient is registered in the study database, any SAE, or follow-up to a SAE, including death due to any cause, that occurs to any subject must be reported within 24 hours to the Sponsor **if is the result of a protocol-specified intervention/procedure**.

- All SAEs occurring from the time a subject is randomized until 90 days after last protocol treatment and;
- any SAE that occurs outside of the SAE detection period (after the 90-days period), if it is considered to have a reasonable possibility to be related to the protocol treatment or study

participation.

- Any secondary malignancy should also be reported in expedited way on a SAE form with the appropriate seriousness criteria.

All reporting must be done by the local principal investigator or authorized staff member (i.e. on the signature list) to confirm the accuracy of the report.

All SAE data must be collected on the study-specific SAE form.

All SAEs must be reported immediately and no later than 24 hours from the time the investigator or staff became aware of the event via fax ([contact]) using the SAE reporting form provided by the sponsor-investigator (exception for fax: site of the sponsor-investigator).

All SAE-related information needs to be provided in English.

All additional documents in local language must be accompanied by a translation in English, or the relevant information must be summarized in a follow-up SAE report form.

The investigator shall record all SAEs on the SAE sub-page of the eCRF.

The sponsor-investigator will re-evaluate the SAE and return the form to the site as required.

Recurrent episodes, complications, or progression of the initial SAE must be reported as follow-up to the original episode, regardless of when they occur. This report must be submitted within 24 hours of the investigator receiving the follow-up information. An SAE that is considered completely unrelated to a previously reported one should be reported separately as a new event.

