#### **11.3.2 Primary Analysis**

The primary analysis will be based on the ITT patient set. Patient characteristics will be presented in a table, separate by treatment group, as number and percentage, mean and standard deviation, or median and interquartile range, as appropriate.

VHI collected over 24 months will be analyzed using a repeated-measures, linear mixed-effects model with a random intercept for the patients and fixed effects for the baseline value, the treatment group, the time points (categorical), interaction terms between treatment group and time points, and randomization stratification factors. We will present the mean VHI difference between the two groups with associated 95% confidence intervals and p-values over all time points (primary outcome) as well as separate for each time point (secondary outcomes) from this model.

JS, GNE, and SPR are measured on a continuous scale and, therefore, will be analyzed using the same approach as for VHI. Jitter and shimmer are expected to show a log-normal distribution and will therefore be log-transformed before the analysis. If the distributions of the other two outcomes also severely deviate from a normal distribution, the measures will be transformed in an adequate way, e.g. by log-transformation. If normality cannot be achieved, measures will be analyzed using a non-parametric Wilcoxon rank sum test, separate for each time point.

Roughness, breathiness, and hoarseness are each assessed on an ordinal scale ranging from 0 to 3. These measures will be dichotomized into 2/3 versus 0/1 and analyzed using mixed-effects logistic regression with a random intercept for the patients and fixed effects for treatment group, the time points (categorical), interaction terms between treatment group and time points, and randomization stratification factors. We will present the odds ratio with associated 95% confidence intervals and p-values over all time points as well as separate for each time point from this model.

The time-to-event outcome loco-regional control will be evaluated using Kaplan-Meier curves and a Cox model adjusted for the randomization stratification factors.

Treatment toxicity at 2 and 5 years will be summarized descriptively for each group, showing the overall number of events as well as number and percentage of patients with events.

Patients will be censored for toxicity assessment at the time of loco-regional and/or distant tumor recurrence.

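### After 90 days, reporting a new cancer to the sponsor depends on unblinded attribution, second primaries have no clear rule, and toxicity censoring ignores a new head and neck cancer

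*Protocol*

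**What the plan says.** Protocol section 10 defines two classes of new cancer by cause. A secondary malignancy "is a cancer caused by treatment for a previous malignancy (e.g., treatment with investigational agent/intervention, radiation or chemotherapy"). A second primary malignancy "is one unrelated to the treatment of a previous malignancy (and is not a metastasis from the previous malignancy"). The same section defines an SAE without regard to cause, as an event "whether or not considered related to the protocol treatment, that" meets one of the listed seriousness criteria.

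Section 10.5 then sets the reporting duties:

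- The lead-in sentence limits 24-hour reporting to SAEs that result from a protocol intervention or procedure.
- The first bullet asks for more: "All SAEs occurring from the time a subject is randomized until 90 days after last protocol treatment and".
- After the 90 days, an SAE is to be reported if a relation to protocol treatment or study participation is reasonably possible.
- For malignancies: "Any secondary malignancy should also be reported in expedited way on a SAE form with the appropriate seriousness criteria". No time limit is given.
- A later sentence tells the investigator to record all SAEs on the eCRF, with no limit of time or cause.

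No reporting rule names second primary malignancies. On toxicity, section 11.3.2 states: "Patients will be censored for toxicity assessment at the time of loco-regional and/or distant tumor recurrence". Section 9.2.2 likewise stops toxicity assessment at recurrence. Neither section mentions a new cancer.

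**The concern.** The trial compares radiation with surgery and follows both arms on one schedule to month 60. A late safety record is comparable between arms only if an event is captured in the same way whatever treatment the patient had. Here the duty to tell the sponsor about a late new cancer depends on attribution by an investigator who knows the treatment. For an irradiated patient, attribution is a genuine question. For a patient who had laser surgery alone, the answer is nearly fixed in advance. Reported late cancers could therefore differ by treatment received for reasons other than incidence.

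The second consequence concerns the toxicity endpoint. A patient treated for a new primary of the head and neck remains under toxicity assessment. Dysphagia, hoarseness or stenosis caused by that treatment would be graded on the Appendix A list and could be counted as toxicity of the randomized arm.

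**Working it through.** The plan gives no figure on this point, so the main check is a reading of the rules.

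**Which rule reaches a new cancer?**

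| Situation | Rule in 10.5 | Result |
|---|---|---|
| Within 90 days of last treatment, either class | All-SAE bullet | Reportable if serious, subject to the narrower lead-in |
| After 90 days, classed as secondary | Malignancy sentence | Reportable, but the class itself presupposes cause |
| After 90 days, relation reasonably possible | Late-SAE bullet | Reportable if serious; depends on the relatedness judgement |
| After 90 days, classed as second primary | Neither late rule, since the class is unrelated to treatment by definition | No duty to report to the sponsor |
| Any time, serious, any cause | eCRF sentence | Read literally, to be recorded |

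The last two rows are the inconsistency. The eCRF sentence covers a late second primary that meets a seriousness criterion, yet the same section describes the time after 90 days as outside its SAE detection period, and its lead-in restricts reporting to results of an intervention. Sites can read this either way.

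**Who judges, and how?** Section 10.3 gives causality to the investigator, and section 6.2.2 says blinding is not possible. In Table 5 the category Possibly needs only a temporal relationship and tolerates another cause.

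**Does another dataset catch the event?** Appendix A, on which the toxicity endpoint rests, has no malignancy item. Section 9.2.3 makes any AE of grade 3 or above an SAE, but refers back to section 10 for reporting. Loco-regional control (section 9.2.2) counts biopsy-proven HNSCC recurrence in the head and neck region without saying how recurrence is told from a new primary.

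**Size, on assumed rates.** The documents give no incidence of new cancers. Inputs: 17 patients per arm (section 11.1); follow-up to month 60, less about 1 month of treatment and the 3-month window, so (60 − 1 − 3)/12 = 4.67 years. Assumptions: a constant yearly rate r of 1%, 2% or 4%, equal in both arms, with no deaths or losses.

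Expected late new cancers per arm, E = 17 × [1 − (1 − r)^4.67]:

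- r = 1%: E = 0.78
- r = 2%: E = 1.53
- r = 4%: E = 2.95

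Suppose further that a share q of 10% to 50% of those in Arm B is judged related, and about none in Arm A (laser surgery alone throughout). Reports to the sponsor from Arm B are E × q; new cancers with no duty to report, over both arms, are 2E − E × q:

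- r = 1%: 0.08 to 0.39 reported, 1.48 to 1.17 not
- r = 4%: 0.29 to 1.47 reported, 5.60 to 4.42 not

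The unreported figures concern reporting to the sponsor. Some of these cancers may still be on the eCRF.

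**Toxicity.** One patient with misattributed toxicity moves an arm's percentage by 1/17 = 5.9 points.

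**The case against.** A reader might infer that late second primaries are lost altogether. The text does not force this. The SAE definition is independent of cause, most new cancers would meet a seriousness criterion, and the eCRF sentence is unrestricted. Within 90 days the all-SAE bullet covers them too.

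A reader might also infer that a late cancer is reportable only if judged to be caused by treatment. That holds for the malignancy sentence, because of the definition. The general late rule asks only for a reasonable possibility, and Table 5 sets that bar low. What stands is that both routes still pass through an unblinded judgement of relatedness.

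A third tempting reading is that ascertainment is unequal by randomized arm. The wording is identical in both arms, and section 8.2.3 allows adjuvant radiotherapy in Arm A. The split follows treatment received: surgery alone against any irradiation.

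The lead-in may have been meant for the time before randomization only, which would remove its conflict with the first bullet. As printed it has a start and no end, so the text does not settle this.

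New malignancy is not a listed outcome, and no comparison of it is planned. A new HNSCC in the head and neck would be biopsied and might be classed as recurrence, which would stop toxicity assessment. These points limit the importance of the matter. They do not remove it: a 5-year toxicity report is a stated secondary outcome, no criteria govern that classification, and an analysis plan cannot recover events that sites did not record.

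**Conclusion.** The point holds as a cheap improvement to the safety data. After 90 days, reporting a new cancer to the sponsor rests on open-label attribution; second primary malignancy is defined and then given no reporting rule; and the sentences of section 10.5 disagree on what is to be captured. Capture of second primaries is therefore inconsistent and may differ between patients treated by surgery alone and those irradiated.

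The toxicity censoring rule covers recurrence but not a new head and neck cancer, so toxicity from treating the latter can be charged to the randomized arm, at 5.9 percentage points per patient.

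The expected number of events is small, about 0.8 to 3.0 per arm, and rests wholly on the assumed rates. The primary endpoint and the sample size are not in question. What is at stake is the completeness and comparability of the 5-year safety record.

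**What to change.** 1. In section 10.5, reconcile the lead-in, the bullets and the eCRF sentence, stating for each the period and the events it covers.
2. Record every new malignancy, secondary or second primary, in both arms to month 60 on the eCRF irrespective of judged cause, with causality as a separate field. Expedited reporting can stay as it is.
3. Add a sensitivity summary of toxicity that excludes or flags events arising after treatment of a new head and neck cancer.

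The cost is a short edit to 10.5 and a few more eCRF entries. No extra visits are needed, since endoscopic follow-up already runs to month 60 in both arms.
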